## Abstract

**Background:**

Diagnostic error in ambulatory care, a frequent cause of preventable harm, may be mitigated using the collective intelligence of multiple clinicians. The National Academy of Medicine has identified enhanced clinician collaboration and digital tools as a means to improve the diagnostic process.

**Objective:**

This study aims to assess the efficacy of a collective intelligence output to improve diagnostic confidence and accuracy in ambulatory care cases (from primary care and urgent care clinic visits) with diagnostic uncertainty.

**Methods:**

This is a pragmatic randomized controlled trial of using collective intelligence in cases with diagnostic uncertainty from clinicians at primary care and urgent care clinics in 2 health care systems in San Francisco. Real-life cases, identified for having an element of diagnostic uncertainty, will be entered into a collective intelligence digital platform to acquire collective intelligence from at least 5 clinician *contributors* on the platform. Cases will be randomized to an intervention group (where clinicians will view the collective intelligence output) or control (where clinicians will not view the collective intelligence output). Clinicians will complete a postvisit questionnaire that assesses their diagnostic confidence for each case; in the intervention cases, clinicians will complete the questionnaire after reviewing the collective intelligence output for the case. Using logistic regression accounting for clinician clustering, we will compare the primary outcome of diagnostic confidence and the secondary outcome of *time with diagnosis* (the time it takes for a clinician to reach a diagnosis), for intervention versus control cases. We will also assess the usability and satisfaction with the digital tool using measures adapted from the Technology Acceptance Model and Net Promoter Score.

**Results:**

We have recruited 32 out of our recruitment goal of 33 participants. This study is funded until May 2020 and is approved by the University of California San Francisco Institutional Review Board until January 2020. We have completed data collection as of June 2019 and will complete our proposed analysis by December 2019.

**Conclusions:**

This study will determine if the use of a digital platform for collective intelligence is acceptable, useful, and efficacious in improving diagnostic confidence and accuracy in outpatient cases with diagnostic uncertainty. If shown to be valuable in improving clinicians’ diagnostic process, this type of digital tool may be one of the first innovations used for reducing diagnostic errors in outpatient care. The findings of this study may provide a path forward for improving the diagnostic process.

**International Registered Report Identifier (IRRID):**

DERR1-10.2196/13151

## Introduction

### Background

Diagnostic errors (defined as missed, delayed, or wrong diagnoses) in primary care affect an estimated 1 in 20 US adults every year [1]. About half of these errors can lead to serious preventable harm, but few interventions have been developed and tested to reduce diagnostic errors in real-world ambulatory care settings such as primary care or urgent care clinics [1-4]. This significant gap in clinical practice carries tremendous public health implications. Most individuals receive care in ambulatory care settings [5]. Diagnosis is particularly challenging in primary and urgent care because of 2 structural factors: (1) the short time duration and pressure to complete visits affects cognition and (2) primary care encompasses the broadest range of clinical concerns, from common diseases to rare conditions [6].

In current usual practice, clinicians at primary care and urgent care clinics commonly diagnose patients independently without collaboration or consultation with other health professionals or the use of health information technology (IT), potentially leading to an increased risk of diagnostic errors [7]. In focus groups about outpatient diagnosis, clinicians identified the use of technology to improve communication among them as a key strategy to enhance timely and accurate diagnosis [8]. In its recent report on diagnostic error, the National Academy of Medicine suggested that health systems employ 2 key strategies that are essential to reducing diagnostic error in the ambulatory care setting: (1) enhance interclinician collaboration and (2) develop and utilize health IT innovations in the diagnostic process [6]. A collective intelligence technology platform could be a promising tool to implement these 2 key strategies.

Collective intelligence is defined as shared or group intelligence that emerges from the collaboration or collective efforts of many individuals. It harnesses the ability of a group to outperform the individual in a variety of cognitive tasks [7]. IT platforms offer the opportunity to connect people and harness their collective intelligence through crowdsourcing—the practice of obtaining input into a task or project by enlisting the services of a large number of people via the internet [9]. In discrete tasks related to medical decision making, such as classification of radiology scans and pathological specimens, collective intelligence technology has been shown to improve accuracy when compared with individual decision making [10,11]. However, the impact of collective intelligence technology on diagnostic accuracy remains unproven in outpatient practice. Studies examining collective intelligence technologies have shown that users are enthusiastic about cross-discipline collaboration and easily obtaining expert feedback but wary of inaccuracies and inefficiency of using a collective intelligence tool [12].

In previous simulation testing, the collectively derived output from a collective intelligence platform outperformed its individual physicians in identifying the correct diagnosis in its assessment of standardized clinical cases [13,14]. However, effective implementation of such a tool in the outpatient setting requires examination of its efficacy and usability in real-world primary care and urgent care clinics.

### Study Objectives

In this pragmatic randomized controlled trial, we will examine the efficacy of a collective intelligence technology platform on improving primary clinicians’ confidence in their diagnostic assessments and their accuracy in making a correct diagnosis. We will also examine clinicians’ perceptions of the usability of the collective intelligence technology platform and their likelihood of using (ie *,* intention to use) such a platform in routine primary care or urgent care practice to assist with the diagnostic process.

### Ethical Approval

This study was reviewed and approved by the institutional review board at the University of California, San Francisco.

## Methods

### Setting and Study Population

We will use a convenience sampling approach to recruit primary care and urgent care clinicians in San Francisco, including clinicians from University of California San Francisco (UCSF) primary care clinics and San Francisco Department of Public Health (SFDPH) health care system, which includes 12 urban safety-net primary care clinics that serve a low-income and racially and ethnically diverse patient population. This system is an integrated care system with primary care clinics throughout the city of San Francisco, including 2 academic clinics that are staffed by UCSF faculty physicians. The clinics also provide urgent care through clinic sessions (half days or entire days) reserved for urgent care visits.

### Intervention

The intervention in this study is the provision of a Web-based collective intelligence output to primary care clinicians within 80 hours of a case presentation to assist them in the diagnostic process for routine clinical cases that do not yet have an established, confirmed diagnosis.

### Collective Intelligence Platform

The Human Diagnosis Project (Human Dx) is a Web-based and mobile collective intelligence platform designed to implement both key strategies for reducing diagnostic error recommended by the National Academy of Medicine—interclinician collaboration and use of health IT in the diagnostic process—by utilizing collective intelligence among clinicians. Clinicians input the relevant details of a clinical case or question into the Human Dx platform. Afterward, any number of clinicians (including peers and specialists) participating on the platform, a minimum of 5 for this study, independently review the case and provide their own differential diagnoses and management plans. Using advanced techniques including prefixed search, autocomplete, and natural language understanding, Human Dx is able to structure clinicians’ clinical assessments and aggregate them to produce collective intelligence [13]. The collective intelligence output consists of (1) a collective differential diagnosis derived from a synthesis of respondents’ differential diagnoses, (2) a collective management plan derived from a synthesis of respondents' management plans, and (3) free-text explanations from respondents of the rationales behind their differential diagnoses and plans (Figure 1). Human Dx has been available since 2014 and has over 21,000 physician and medical student users who have solved or entered at least one case. To date, there are over 282,000 entered or solved cases on the platform.

**Figure 1 figure1:**
[figure not shown]
Screenshot of a collective intelligence output from the Human Dx platform for a clinical case. The columns display the collective intelligence output with the differential diagnosis, plan, and rationales. The interface is interactive – users can hover or click to see details of the case that was entered and details on the output differential diagnosis, rationales, and plan.

### Study Design

This is a pragmatic randomized controlled trial in which primary care clinicians are followed over 4 to 8 weeks to identify a minimum of 20 cases, for each clinician, with potential diagnostic uncertainty. Half of the selected cases for each clinician will be randomized to the intervention and the clinician will receive a collective intelligence output for those cases. Human Dx will generate collective intelligence for the remaining (control) cases, but clinicians will not receive the collective intelligence output for these cases (Figure 2).

**Figure 2 figure2:**
[figure not shown]
Workflow for participants. At baseline clinicians complete their normally-scheduled clinical sessions and complete their notes in the electronic health record. A study scribe examines each note and determines inclusion based on a study rubric. The study scribe enters the case into the collective intelligence (CI) platform within 24 hours and online contributors provide their own assessments to generate a CI within 36 hours. The CI output is sent to the study team, who randomize each case, and send the CI output to participants for cases randomized to the intervention. Participants receive a post visit questionnaire for all study cases (intervention and control).

### Selection, Entry, and Randomization of Clinical Cases

For the purpose of this study, clinicians will not enter their own cases. For case entry, we will utilize study scribes who are medical doctors (MD) in their second or third year of internal medicine residency at UCSF. These scribes are analogous to intended real-world users of the Human Dx platform (ie, primary care and urgent care medical providers). On the basis of each participant’s clinical schedule, study scribes will access the electronic health record within 24 to 36 hours after the participant’s clinic session and identify cases that meet the study selection criteria (see below).

Study scribes enter cases that meet the inclusion criteria into the collective intelligence platform. A minimum of 5 clinicians will act as *contributors* who review and comment on each case in the collective intelligence platform within 24 to 36 hours of case entry, generating a collective intelligence output. The contributors recruited by Human Dx for this study were US-based attending-level physicians in internal medicine or family medicine. They were recruited from an existing pool of active Human Dx users (ie, they had solved at least one case within 3 months of being recruited for the study), which does not include any of the clinician participants in our study population. They are not affiliated with our study team and are blinded to our study procedures including case randomization (Figure 2).

Once the collective intelligence output becomes available for a case, the study team randomizes it to the intervention or control cases. The study team assigned each case a unique study identification number for tracking purposes. Using a random number generator in blocks of four, we will randomize half of the cases, for each clinician, to an intervention group in which the clinician will receive a collective intelligence output between 60 and 80 hours from the time the clinician saw the patient in the clinic (ie, within 24-36 hours of case entry). For cases randomized to the controlled group, Human Dx will generate collective intelligence, but it will not be shared with the clinician. Clinicians will complete an online postvisit questionnaire for all of their cases (control and intervention) that provides their initial impressions of the case (eg, differential diagnosis and perceived case difficulty) and level of diagnostic confidence. The questionnaire for cases assigned to the intervention group includes additional questions that the clinician will answer after reviewing the collective intelligence output to assess the effect of the output on their diagnosis, plan, and confidence. The study scribes and the *contributors* on Human Dx will be blinded to case randomization.

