### Case Selection Criteria

Scribes will select cases based on a rubric designed to capture diagnostic uncertainty. If a case meets any of the following criteria, it will be entered into the Human Dx platform: (1) a new symptom or abnormality in laboratory, physical exam, or radiographic finding; (2) a recurrent symptom or abnormality in laboratory, physical exam, or radiographic finding without a clear diagnosis or etiology; (3) a pending diagnostic test ordered to evaluate a new or unresolved condition; (4) empiric treatment provided without complete diagnostic certainty; and (5) if the clinician submitted a request for electronic consultation from a specialist within the health network for a diagnostic or management problem. Clinicians may also flag a case for review that the scribes will enter into the Human Dx platform whether or not it meets the above rubric’s selection criteria.

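### One fixed block of four per clinician, allocated by an unblinded study team that already holds each output, leaves a third of allocations predictable to that team

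*Protocol article*

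**What the plan says.** The section Selection, Entry, and Randomization of Clinical Cases gives the method: "Using a random number generator in blocks of four, we will randomize half of the cases, for each clinician, to an intervention group". No other block size is mentioned. Study Design gives the same ratio within clinician: "Half of the selected cases for each clinician will be randomized to the intervention".

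The same Selection section fixes the order of steps: "Once the collective intelligence output becomes available for a case, the study team randomizes it to the intervention or control cases". The Figure 2 caption agrees: "The CI output is sent to the study team, who randomize each case, and send the CI output to participants". So the team that allocates has the output first, and it then forwards the output for intervention cases.

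Cases get into the trial earlier, through other people: "Study scribes enter cases that meet the inclusion criteria into the collective intelligence platform". The scribes and the contributors "on Human Dx will be blinded to case randomization". The article does not list the study team or the clinicians as blinded. Under Case Selection Criteria, clinicians have one way to add cases: "Clinicians may also flag a case for review that the scribes will enter into the Human Dx platform whether or not it meets" the rubric.

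**The concern.** Three features come together: one small block size, an allocator who knows the earlier arms because the same team dispatches the outputs, and sight of the output before allocation. Each is tolerable alone. In combination, a team member with two or more outputs waiting for the same clinician could know or guess the next arm while looking at what each output contains. The article states no rule for which waiting case takes the next slot.

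The primary outcome makes this matter. It is self-reported confidence, rated in intervention cases after the output has been viewed, so it should respond to how clear or convincing the output is. If more persuasive outputs, or cases that look easier to resolve, moved towards the intervention arm, the confidence contrast would be affected and the time-to-diagnosis contrast could be. The primary model in the Analysis Plan contains only intervention status, with clustering on clinician, so it has no case-level covariate to offset such a drift.

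**Working it through.** **Inputs.** Block size 4 (Selection section). Ratio 1:1 within clinician (Study Design, Selection section). 33 clinicians with about 20 cases each, 10 per arm, 660 in total (Sample Size Justification). Blocking within clinician is the natural reading, because it delivers half of each clinician's cases, but the article does not say so outright.

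**The plan's own figures.** 33 × 20 = 660. 20 / 4 = 5 complete blocks per clinician, and 5 × 2 = 10 cases per arm. Both agree with the article.

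**Share of allocations fixed by earlier ones.** A 2:2 block of four has 4! / (2! × 2!) = 6 equally likely sequences.
- In 2 of them (both of one arm, then both of the other) slots 3 and 4 are fixed.
- In the other 4 only slot 4 is fixed.
- Mean number fixed = (2 × 2 + 4 × 1) / 6 = 8/6 = 1.333 of 4 = 33.3%.
- Per clinician: 20 / 3 = 6.7 cases. Overall: 660 / 3 = 220 cases.

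**Best-guess rate.** The observer guesses the arm with fewer allocations so far in the block and tosses a coin when they are equal.
- Slot 1: 1/2.
- Slot 2: 2/3.
- Slot 3: (1/3 × 1) + (2/3 × 1/2) = 2/3.
- Slot 4: 1.
- Sum = 17/6 = 2.833 of 4 = 70.8%, against 50% with full concealment.

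**What a choice of order could do.** Suppose the last slot of a block is known to be intervention and two outputs are waiting. The case put in that slot goes to intervention with probability 1. The other opens a new block and goes there with probability 1/2.

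**Effect of mixed block sizes.** This was simulated with 10,000 runs of 20 cases, sizes drawn with equal probability, and an observer who knows the possible sizes but not their order.

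| Block sizes | Certain allocations | Best guess right |
|---|---|---|
| 4 only | 33.3% | 70.8% |
| 4, 6 | 5.8% | 68.5% |
| 2, 4, 6 | 3.7% | 69.6% |
| 4, 6, 8 | 2.3% | 67.1% |

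Mixing removes most of the certainty, because the observer no longer knows where a block ends. It hardly lowers the success of guessing. The order of assignment is therefore the main thing to control.

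**The case against.** A reader might infer that concealment fails in this trial, or that a third of allocations were in fact known. The documents do not support that. The article does not say who generates or holds the list or whether case handlers can see it, and a condensed article may leave this to the full protocol. The one-third figure applies only to someone who knows the block size, the boundaries and every earlier arm for that clinician. The study team could know these; nothing shows that anyone tracked them.

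Predictable blocks do most harm when the person deciding on entry can foresee the arm. Here blinded scribes enter cases by rubric from consecutive sessions, before an output exists. The Figure 2 caption has each case randomized, and no step is described for dropping or reordering cases. This largely answers concerns about entry. It does not answer the concern about the order of outputs already in hand.

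Clinician flagging is also a weak route. Scribes enter qualifying cases alongside flagged ones, so clinicians do not control position in the sequence. Outputs reach them 60 to 80 hours after the visit, so recent arms may be unknown when a case is flagged.

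Nor would any resulting bias be beyond all adjustment. Initial impressions and perceived difficulty are collected in both arms before any output is viewed, and the Exploratory Analyses adjust for them. That adjustment is outside the primary model and covers case difficulty, not output quality.

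The criticism survives because it concerns choices the article states: the single block size, and allocation with the output in hand. A concealed list in an unseen document would lower the risk but would not change either choice.

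**Conclusion.** The point holds as a conditional weakness for which the article describes no safeguard. A team member with full knowledge of the sequence so far could be certain of one third of allocations (about 220 of 660) and guess 70.8% correctly, while holding the outputs. The open route is the order in which outputs that are ready together are assigned.

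These figures assume 2:2 blocks run within clinician and 20 cases each. They measure predictability, not bias: the documents give no basis for quantifying an effect on confidence or time to diagnosis, and none is claimed. The point is a cheap improvement, not an error that undermines the trial.

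**What to change.** **Main change.** Generate each clinician's list in advance and keep it concealed from those who handle outputs. Assign cases strictly in order of the scribe's entry time stamp, tied to the study ID, before anyone on the team opens the output. Judge a case ready only by whether an output with at least 5 contributors exists, never by its content.

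**Secondary change.** Use randomly mixed block sizes, for example 4 and 6. They supplement the ordering rule and cannot replace it.

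**Cost.** A regenerated list and one operating rule. A clinician's last block may be incomplete, so that clinician's arms may differ slightly, by at most three cases with blocks up to six. Strict entry order also means either a short wait for slow outputs or allocating a few cases before their output is complete. The wait has a limit: on the Selection section's outer times, 36 hours to scribe review plus 36 hours to output leaves 80 − 72 = 8 hours before the end of the delivery window.

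**If enrolment is already complete.** The Results section reports data collection finished as of June 2019. In that case, report who held the list, who could see it and whether allocation followed entry order. Compare entry time stamps with allocation order within clinician and report any departures.

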#### Exploratory Clinical Outcomes

We will measure and analyze specified, additional outcomes that are relevant to the diagnostic process. We will define diagnostic accuracy as having the correct diagnosis listed in the top 3 answers of the collective intelligence output (for intervention cases) or in the top 3 of the clinician’s list of possible diagnoses collected via survey data (for control cases). In addition, we will measure the number of diagnostic tests related to the initial complaint, ordered by the clinician within 30 and 90 days of the case presentation, and the number of unexpected visits (drop-in, urgent care, or emergency room) related to the initial presentation within 14 and 30 days of the index visit. Unexpected visits have been associated with higher risk of diagnostic error [1]. We refer to these as exploratory outcomes because we expect them to be highly variable both within and between clinicians and do not know whether we will have the statistical power to analyze them. Descriptive analyses of these outcomes may generate hypotheses for future study.

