#### Handling of Missing Data

Our general approach to missing data will be multiple imputation. It is possible that our primary outcome of diagnostic confidence will have a level of missing data, as it will depend on the response rate to survey questions. In addition to multiple imputation under the standard assumption that data are missing at random, given the covariates and outcomes that are observed, we will also implement sensitivity analyses using imputation under plausible missing-not-at-random scenarios. To maximize survey completion rates and thereby minimize the level of missing data, we will send 3 email reminders at 3 days, 7 days, and 14 days if the initial survey request was not completed. We will leave hard copies of the survey in clinicians’ mailboxes if the participants have not completed the online survey after the 3 email reminders.

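### The exploratory accuracy comparison sets a platform list fixed at case entry against a clinician list recalled one to about 16 days later, so late test results may inflate control accuracy through hindsight

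*Protocol article*

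**What the plan says.** All references are to the protocol article.

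- **What is scored** (*Exploratory Clinical Outcomes*). In one arm accuracy means "having the correct diagnosis listed in the top 3 answers of the collective intelligence output (for intervention cases"; in the other it means the correct diagnosis "in the top 3 of the clinician’s list of possible diagnoses collected via survey data (for control cases".
- **When the platform's information is fixed** (*Selection, Entry, and Randomization of Clinical Cases*). "study scribes will access the electronic health record within 24 to 36 hours after the participant’s clinic session" and enter the eligible cases. Contributors work from that entry, and no later update of it is described.
- **When the clinician is asked** (same section). A case is randomised only once its output is available. For intervention cases the output reaches the clinician 60 to 80 hours after the visit. *Postvisit Questionnaires* describes emails that differ by arm, so neither can precede randomisation. If there is no reply, "we will send 3 email reminders at 3 days, 7 days, and 14 days" (*Handling of Missing Data*). Hard copies follow, with no closing date stated.
- **What the clinician is asked for.** "Clinicians will complete an online postvisit questionnaire for all of their cases (control and intervention) that provides their initial impressions of the case". The stated safeguard is that these questions come before the clinician views the output.
- **Which cases enter** (*Case Selection Criteria*). One of the five criteria is "a pending diagnostic test ordered to evaluate a new or unresolved condition".
- **Reference diagnosis.** Chart review at 6 months; cases still uncertain then are excluded.

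**The concern.** The two lists being compared do not share an information date. A result that posts after the scribe opened the record can reach the clinician before the questionnaire is answered, but it cannot reach the contributors. Asking for initial impressions states an intention. It does not stop a clinician who has since seen the result from recalling the right diagnosis as an early thought. Answering before viewing the output guards against a different influence.

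The protocol sees the hazard. *Primary and Secondary Outcomes* names the time taken to receive test results among the outside factors that can confound accuracy. Yet the covariates in *Exploratory Analyses* include neither pending-test status, nor result availability, nor questionnaire completion time. Randomisation balances when results arrive, but that does not help when the scored list can absorb a late result in one arm only.

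At stake is the reading of the accuracy result. Accuracy is an exploratory outcome, but improving it is one of the study objectives, and the abstract's conclusion says the study will determine efficacy for it.

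**Working it through.** The protocol gives no expected accuracy, power or sample size for this outcome, so there is no planned figure to reproduce. Two things can be checked: the length of the gap, and how the bias would scale.

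**1. Gap at the initial request.** Inputs: record opened 24 to 36 h after the visit; output delivered 60 to 80 h after the visit.

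- Shortest: 60 − 36 = 24 h (1.0 day).
- Longest: 80 − 24 = 56 h (2.3 days).

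**2. Gap at the third reminder.** Add 14 days: 15.0 to 16.3 days. Hard copies extend it further.

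**3. How firm these figures are.**

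- The 60 to 80 h window is stated for intervention cases only. For control cases it is inferred from the rule that randomisation waits for the output.
- The protocol also glosses delivery as falling within 24 to 36 h of case entry. On that reading the gap is at most 36 h at the request, and 15.0 to 15.5 days at the third reminder when counted from 24 to 36 h.
- The Figure 2 legend puts entry within 24 h of the visit. If entry were almost immediate, the gap could reach 80 h (3.3 days), or 17.3 days at the third reminder.
- The steps as described sum to 24 + 24 = 48 h up to 36 + 36 = 72 h, against the stated 60 to 80 h.

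These readings move the figures by hours to about a day. None of them closes the gap.

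**4. How a bias would scale.** Let c be the clinician's top-3 accuracy without later results. Let q be the share of control lists in which a settling result arrived in the gap and the final diagnosis was then listed. If affected cases have the same c as the rest, control accuracy rises by q(1 − c), and the platform-minus-clinician difference falls by the same amount. Neither c nor q is in the protocol; both are assumed here.

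| q | c = 40% | c = 60% | c = 80% |
|---|---|---|---|
| 0% | 0 | 0 | 0 |
| 5% | 3 | 2 | 1 |
| 10% | 6 | 4 | 2 |
| 20% | 12 | 8 | 4 |
| 30% | 18 | 12 | 6 |

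Entries are percentage points. For scale, at c = 60% a true platform advantage of 10 points would be cancelled at q = 0.10 / 0.40 = 25%. That advantage is hypothetical as well.

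**The case against.** A reader might infer that clinicians are simply credited with results the platform never saw, and that the comparison is therefore biased against the platform. The documents do not support that, for three reasons.

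- **The form asks for initial thinking.** The plan does not intend to use later results, so the exposure is hindsight in recall. How well the form ties answers to the visit depends on its wording in Multimedia Appendix 1, which is not shown. A gap of two weeks applies only to clinicians who let every earlier request pass, and their share is not given.
- **The net direction is open.** The reference diagnosis comes from the 6-month chart. In intervention cases the clinician had been sent the platform's output, which can pull the reference towards the platform. Excluding cases still uncertain at 6 months adds a selection of unknown effect.
- **The outcome is exploratory.** The protocol claims no power for accuracy and treats such analyses as hypothesis generating. The primary outcome, the secondary outcome and the sample size are untouched.

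All three stand, and they limit the point. They do not remove it: a second bias of unknown size in the other direction makes the comparison harder to read and cannot be relied on to cancel this one.

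It is also fair to say that the planned before-and-after comparison within intervention cases largely escapes the problem, because both answers come from the same questionnaire. Scoring the clinicians' own lists in both arms would also largely equalise information time. Scoring both lists in every case would not, because the platform's list would still be the older one.

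**Conclusion.** The point holds in limited form. The platform's list and the control clinician's list are taken at different information times: about 1 to 2.3 days apart at the initial request and about 15 to 16 days at the third reminder, with control timing inferred. In cases with a pending test, a result posting in that interval may raise control accuracy through hindsight, and nothing in the article controls for it. Taken alone, this route works against the platform. Its size is unknown: the 0 to 18 points above rest wholly on assumed c and q, and with q = 0 there is no bias. The net direction of error in the accuracy comparison is not established. This calls for a cheap improvement to an exploratory analysis.

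**What to change.** 1. **Abstraction.** During chart review, record the date of the confirmatory result and the date of the documented diagnosis separately, even when empiric treatment came earlier. Time to diagnosis needs only the earliest of the three events, and empiric treatment is itself an entry criterion, so the other two dates may otherwise be lost. Record the questionnaire completion date as well.
2. **Added comparison.** Repeat the accuracy comparison in cases with no confirmatory result and no newly documented diagnosis between case entry and randomisation. Membership is settled before allocation, so the randomised contrast is kept. It does not cover results that arrive between randomisation and a late reply.
3. **Sensitivity analysis.** Repeat it in cases with neither date before questionnaire completion. Label this as post-randomisation selection: the intervention questionnaire is longer, so completion time may differ by arm.
4. **Conclusion.** Word the accuracy conclusion to reflect the difference in information time and the open net direction.

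Scoring the clinician from the index-visit note is not a good substitute. Notes are not written as ranked lists and may hold fewer than three diagnoses, which would penalise the clinician and bring its own bias.

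**Cost.** Some loss of precision in the restricted analyses and a little extra abstraction. The article reports data collection complete as of June 2019, so completion dates may have to come from survey records. The article does not say whether these were kept, nor how hard copies were dated.
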